### Data collection

Our approach uses a stepped-wedge, cluster randomized control design to test the strategies used by the practice [87]. We will randomize three FQHC’s with three practices each (*n* = 9 practices), who meet eligibility criteria requirements, to begin the intervention first, second, or third. All practices within a given FQHC are in the same cluster. The design involves random and sequential crossover of an FQHC’s 3 practices from the control period to implementation of the facilitator-driven strategies until all are exposed [87]. We will assess primary and secondary effectiveness outcomes at baseline and every three months afterward. We powered the trial based on the primary outcome of HPV vaccine initiation and completion of 11–12 year olds.

#### Measurement and evaluation

We will assess primary and secondary effectiveness outcomes during the control period and after every 3 months, using de-identified, randomly selected, EHR data from patients aged 11–12 and 13–17 per practice. We will incorporate the general guidelines of the Immunization Quality Improvement for Providers protocol developed by the CDC [73]. The protocol recommends collecting 50 EHRs for every 150 patients. A trained information technology specialist, who is employed at each site (PVHC, CHN, and SBCHC), will provide de-identified, randomly selected, EHR data to the data manager. The external facilitator will be responsible for evaluation activities related to HCP, immunization navigators, and practice staff. Immunization navigators will enter and store process evaluation data onto REDCap. We will use these data to evaluate the clinical practice plan and track immunization uptake and dose compliance through the EHR. Implementation outcomes will be assessed using pre-post surveys in the baseline assessment and EHR reports. We will use observational data in the form of monthly meeting notes and external facilitator debriefs to assess the complexity associated with *context* and the *recipients* involved in the implementation at the practice settings as they influence implementation.

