#### Development and implementation of the clinical practice plan

This strategy consists of facilitator-led HCP education, assessment and feedback, and technical assistance. The external facilitator will conduct six modules over three months. HCP will complete a brief evaluation to receive continuing education units and evaluate the overall program after each module. In modules 5–6, the external facilitator will assist the implementation team in creating a clinical practice plan (or plan), and afterwards provide technical assistance plus assessment and feedback during its implementation. The external facilitator will also train immunization navigators to implement the plan, and conduct booster trainings and site visits every six months, to ensure performance does not deteriorate.

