### Data collection

We will conduct the following assessments at each practice site:*HCP and staff surveys*. The FQHC’s designee will e‐mail an invitation with an embedded link to all providers and staff at each practice site to participate in a brief survey [74–77]. The survey measures HPV vaccine knowledge, attitudes, provider confidence responding to vaccine hesitant parents, and both provider-and practice-level behaviors regarding HPV vaccination.*Implementation Team Remote Interviews*. The FQHC’s designee will recruit the practice implementation team and encourage participation. The external facilitator will conduct interviews focusing on conducting a practice readiness assessment [78], facilitating a discussion around their practice level data, and identifying challenges to achieving target vaccination rates.*Observations*. Research staff will conduct observations of patient flow and clinical workflows to determine how to best implement strategies in the practice setting. Research staff will take detailed notes of what occurs during the visit, how a patient is identified as needing the HPV vaccine, and the process the patient goes through for receiving (or not receiving) the vaccine.*Parent surveys*. Research staff will conduct a cross-sectional, self‐administered, REDCap survey evaluating parents’ HPV vaccine knowledge, behaviors, general and HPV related vaccine hesitancy, self-efficacy in and reducing perceived barriers to vaccinating their child, experience with provider’s HPV vaccine recommendation, and practice service [35, 79–83], Practice staff will invite parents of children ages 11–17 who are scheduled for well-child check during the baseline and post assessment periods and *have not received the HPV vaccine* to participate.

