#### Implementation outcomes

We will measure the implementation outcomes at the level of the provider (increase the number of providers giving HPV vaccine recommendations and their confidence in recommending the vaccine to hesitant parents), practice (increase in the number vaccine doses provided per practice and increase in the number of reminders provided to patients for HPV vaccine dose completion), and at the level of the patient/parent (increase parental confidence and reduce perceived barriers in vaccinating their children). We will conduct the HCP/staff and parent surveys 12 months after project activities start. In addition, we will also use the i-PARIHS framework [63] to gather observational data during the implementation period, which will enable us to track and review the progress of each practice.

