### Data collection

Twelve months after implementation, we will also conduct semi-structured interviews with implementation team to identify key factors that influence sustainability of the strategies over the next three-five years. We will use interviews to gain in-depth insight and explore the real-world complexity associated with sustaining interventions in FQHCs, as recommended in previous literature [89, 90]. Informed by the ISF [89] and the observational data collected during the implementation period, we will work with our study team to develop an interview guide consisting of open-ended questions. Similar data collection procedures will be followed as described in baseline assessment for implementation team interviews.

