### Consent process

Providers, staff, and parents will complete electronic* s*urveys remotely or in person. Research staff will obtain informed consent before pre-post surveys and document consent in REDCap. For remote interviews, research staff will obtain verbal consent from interviewees via video conference and document consent in REDCap. The participants for both surveys and interviews will receive a copy of the consent form via email. See Supplementary Files 4-7.

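### The facilitator who delivers the strategies appears also to conduct the 12-month sustainability interviews, and nothing keeps individual survey answers or transcripts from that person

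*Protocol article*

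**What the plan says.** **Delivery.** Under Development and implementation of the clinical practice plan: "The external facilitator will conduct six modules over three months". The same section says: "The external facilitator will also train immunization navigators to implement the plan, and conduct booster trainings and site visits every six months". The facilitator also helps each team write its plan and then supplies technical assistance, assessment and feedback. Section 2 (implementation) adds monthly meetings through the first year.

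**Evaluation.** Under Measurement and evaluation: "The external facilitator will be responsible for evaluation activities related to HCP, immunization navigators, and practice staff". The activities are not defined. The same paragraph also says: "Implementation outcomes will be assessed using pre-post surveys in the baseline assessment and EHR reports".

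**Baseline interviews.** Data collection under section 1 (baseline assessments) says: "The external facilitator will conduct interviews focusing on conducting a practice readiness assessment". The same list gives the observations and the parent surveys to research staff.

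**Twelve-month interviews.** Data collection under section 3 (sustainability) puts the interviews in the first person plural and then says: "Similar data collection procedures will be followed as described in baseline assessment for implementation team interviews". On consent for remote interviews, the Consent process section says: "research staff will obtain verbal consent from interviewees via video conference and document consent in REDCap".

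**Provider-level outcomes.** Under Implementation outcomes: "increase the number of providers giving HPV vaccine recommendations and their confidence in recommending the vaccine to hesitant parents".

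**The concern.** The sustainability component asks implementation-team members what will help or hinder the survival of strategies that the article itself labels as facilitator-led. If the facilitator asks the questions, respondents are speaking to someone who has taught, advised and met with them for about a year. People in that position tend to soften or leave out criticism, above all criticism of the facilitation.

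Aim 3 is at stake. The interviews are a main source for it, and the Discussion presents their product as the factors that the implementation team perceives. A one-sided account would make the strategies look easier to sustain than they are, and the article intends its findings to inform wider dissemination and scale-up.

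A lesser issue concerns the provider survey. The person responsible for evaluation of the providers is also their coach, and providers are nowhere told that the coach will not see their individual answers.

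**Working it through.** No arithmetic on error rates or power applies. The check is to trace who delivers the strategies, who collects each kind of data, and who handles it afterwards.

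1. **Delivery.** Modules, navigator training, boosters, site visits, help with the plan, and technical assistance are all given to the external facilitator. This is explicit.

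2. **Baseline interviews.** The facilitator is named as interviewer. The same list names research staff for other tasks, so the article does distinguish the two roles.

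3. **Twelve-month interviews.** No interviewer is named. The text refers back to the baseline implementation-team interviews, where the only named interviewer is the facilitator. The Consent process section gives research staff the consent step and does not say who asks the questions. The pilot section counts the facilitator as part of the research team, so the first person plural does not exclude that role. The facilitator as interviewer is therefore an inference, but the natural one, and nothing in the article contradicts it.

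4. **Number of interviews.** The recruitment section plans 4 implementation-team members in each of 9 practices: 4 × 9 = 36. Under the reading in step 3, all 36 are affected. If the full protocol names someone else, none are.

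5. **After collection.** Analysts code the transcripts separately and reach consensus. The section 3 analysis works from respondents' words and from how often, how widely and how intensely a concept appears. Independent coding guards against selective reading of a transcript. It cannot restore a criticism that was never voiced.

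6. **Linked source.** Facilitator debriefs are part of the observational data, and those data shape the 12-month interview guide. Two of the qualitative sources thus pass through the same person.

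7. **Provider and staff survey.** The planned numbers are 4 × 9 = 36 providers and 5 × 9 = 45 staff. The health center's designee e-mails the link, research staff obtain consent, and research staff summarise the answers. The facilitator is not shown to collect these data. The data management section covers identifiers and secure storage in general terms, and does not say that the facilitator is denied access to individual responses.

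8. **Effectiveness outcomes.** Initiation and completion come from randomly selected, de-identified records supplied by an information technology specialist employed at each site. The facilitator has no part in that step.

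**The case against.** The strongest reply has four parts.

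**The evaluation sentence is vague.** It stands next to a sentence on process evaluation data, and implementation outcomes get their own sentence later. It could mean only the brief evaluation after each module together with the assessment and feedback that belong to the intervention. This is a possible reading. However, the module evaluation is already described elsewhere, and the sentence stands under a heading on measurement. The ambiguity is a reason to define the role.

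**The interviewer is not stated.** The cross-reference may cover only recruitment through the designee and the remote format, and an article may leave interviewer assignment to the full protocol. This stands as a limit on certainty, and the number of affected interviews is conditional on it. It does not remove the point, because the article does fix a procedure by reference and that procedure names one interviewer.

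**The interviews are not a rating of the facilitator.** They cover funding, staffing, leadership, fit and partnerships as well. This stands in part: answers about funding or policy are little affected. Answers on training, on implementation process and on fit of the strategies are closer to the facilitator's own work.

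**Provider outcomes are collected at arm's length.** This stands. A reader might infer from the evaluation sentence that the facilitator personally gathers provider recommendation and confidence. The survey route in step 7 does not support that. Research staff also survey parents about their experience of the provider's recommendation, which gives a second source. Nor can a bias that fails to cancel between baseline and follow-up be claimed for the interviews. No pre-post comparison of them is planned: the baseline interview assesses readiness, and the later one uses a separate guide.

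**Conclusion.** The point holds in a limited form. The dual role of deliverer and evaluator is written in the article. On the natural reading it extends to all 36 interviews held twelve months after implementation, and the likely direction of bias is in favour of the strategies. This rests on two assumptions: that the reference back to baseline includes the interviewer, and that respondents are less frank with the person who coached them. The article gives nothing from which to calculate the size of the effect, and any percentage would be invented.

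For provider recommendation and confidence, the remaining exposure is the undefined evaluation role together with the absence of any statement that individual answers are withheld from the facilitator. Some self-report bias would persist whoever handles the survey. The primary and secondary vaccination outcomes are not affected.

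The change should be made before the 12-month interviews, because later analysis cannot correct what was withheld during collection.

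**What to change.** Two wording changes are enough.

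- **Section 3, Data collection:** state that the 12-month interviews are conducted by existing research staff other than the facilitator. The reference to the baseline procedure can stay for recruitment and format.
- **Measurement and evaluation:** define the facilitator's evaluation role as process data only (module evaluations, assessment and feedback, debriefs). State that individual provider and staff survey answers and interview transcripts are not shared with the facilitator, and tell respondents so.

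The baseline readiness interview can remain with the facilitator, since its findings are used to tailor the intervention. If reassignment proves impossible, the dual role should be reported as a limitation of the aim 3 findings.

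The cost is a reassignment of interview time among people already in the study, with no new post. The small downside is an interviewer who knows the practice less well. The facilitator's input to the interview guide can offset that.

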**Methods:**

This proposal considers the HPV vaccine as the evidence-based intervention and describes the rational and study design for “**TRU**sted h**E**alth **SY**stem implementatio**N** strat**EGI**es to increase vaccination (TRUE SYNERGI)”, a hybrid type 2 study that uses previously-piloted implementation strategies (i.e., practice facilitation, provider education, among others) to influence provider recommendations (implementation outcome) and practice-level vaccination rates (effectiveness outcome). To test whether these facilitator-driven implementation strategies influence our implementation and effectiveness outcomes, we will use a stepped-wedge cluster randomized trial and randomize three FQHCs (*n* = 9 practices, 3 per FQHC) to three clusters. We will conduct baseline assessments at each practice, which will provide data to assist the practice facilitator in engaging with the providers and leadership to develop a tailored implementation plan for each practice. In addition, we will employ theory-guided, qualitative methods, to assess the complexity associated with context and the recipients involved in the implementation of strategies in practices, along with sustainability.

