**Fig. 2 Fig2:**
[figure not shown]
Federally Qualified Health Center (FQHC) and participant timeline

We will test whether facilitator-driven provider- and practice-level implementation strategies increase provider recommendations and vaccination rates in three practices per FQHC. To ensure retention of the FQHCs and their staff during the trial, our project emphasizes active engagement using a participatory approach of the HCP and staff at each practice to increase capacity, assess barriers and gaps in vaccination services, and develop clinical practice plans. We have also integrated into our project plan continual assessment and feedback on performance indicators to provide ongoing quality control for participating practices. To ensure the sustainability of the program beyond funding, we will enhance the capacity of the FQHCs by providing trainings, technical assistance with implementing and adopting clinical practice plans, and developing new tools (e.g., provider reminders, patient reminders/recalls) to integrate into their existing practice systems. The multi-faceted approach described in our project plan has the potential to result in the adoption of provider- and practice-level evidence‐based strategies in practices, which will improve HPV vaccination (initiation and completion) rates among their adolescent patients.

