### Analyses

Data collection and analysis will occur separately for each method, and we will triangulate and organize these data, using i-PARIHS. For the HCP/staff and parent surveys, research staff will use simple univariate and bi‐variate analyses to summarize the data in SPSS. We will utilize a content analysis [84, 85] approach for implementation team interview data. We will develop themes using an iterative process where analysts use conceptual labels (or codes) to categorize discrete concepts. Analysts will independently code transcripts and then meet to discuss emerging themes, discussing disputed sections until reaching consensus about coding categories. Based on observation notes, research staff will create a flowchart representing how the practice operates, the amount of time patients spend at any given point during their visit, and who the patient encounters. Guided by i-PARIHS’ *Outer Setting (e.g.,* participant needs and resources, external policies and incentives) and *Inner Setting (e.g.,* readiness for implementation, leadership engagement, available resources) contextual domains, we will triangulate the data and create summary reports.

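### The article says the stepped wedge tests the implementation outcomes, but it assesses them with pre-post surveys and undenominated counts, and its only period-adjusted model covers the binary HPV outcomes

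*Protocol article*

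**What the plan says.** **What is claimed.** The abstract's Methods paragraph states: "To test whether these facilitator-driven implementation strategies influence our implementation and effectiveness outcomes, we will use a stepped-wedge cluster randomized trial". It names provider recommendations as the implementation outcome and practice-level vaccination rates as the effectiveness outcome. The Recruitment, sample size, and retention plan (text after Fig. 2) repeats the aim: "We will test whether facilitator-driven provider- and practice-level implementation strategies increase provider recommendations and vaccination rates in three practices per FQHC".

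**What is specified.**
- Measurement and evaluation: "Implementation outcomes will be assessed using pre-post surveys in the baseline assessment and EHR reports".
- Implementation outcomes, provider level: "increase the number of providers giving HPV vaccine recommendations and their confidence in recommending the vaccine to hesitant parents".
- Implementation outcomes, practice level: "increase in the number vaccine doses provided per practice and increase in the number of reminders provided to patients for HPV vaccine dose completion". The Conceptual framework section also lists these as numbers, without a denominator.
- Implementation outcomes, timing: "We will conduct the HCP/staff and parent surveys 12 months after project activities start". Together with the baseline assessment this makes two survey waves.
- Section 2, Data collection, and Measurement and evaluation: three-monthly assessment is stated for the primary and secondary effectiveness outcomes only.
- Statistical analysis plan: the mixed model with fixed effects for time and intervention and a random practice effect is stated for the binary HPV outcomes.
- Section 1 (baseline assessments), Analyses: "For the HCP/staff and parent surveys, research staff will use simple univariate and" bivariate analyses. This is the only survey analysis described, and it sits in the baseline section.

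**The concern.** A stepped wedge protects against secular change because practices still in the control condition are observed in the same calendar periods as practices already exposed, and the model adjusts for period. An outcome measured once before and once after each start, and compared as such, has no such protection.

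Counts bring a second problem. The number of doses rises with the number of adolescents seen. The number of providers recommending changes when providers leave or join, and the Discussion itself names clinical staff turnover as a potential problem.

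In a hybrid type 2 trial, provider recommendation is one of the two outcomes the abstract puts forward. A reader of the results would take a reported improvement as a randomised finding when the stated assessment cannot support that.

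**Working it through.** **1. What the stepped-wedge calculation covers.** Sample size justification gives 30 × (15 − 1) × 9 = 3,780 subjects. I recomputed Table 4 from the Hussey-Hughes variance: fixed period effects, random practice intercept, total variance p(1 − p), ICC as stated, and minimum detectable difference = (1.96 + 0.84) × SE. Table 3 is not shown, so the schedule is assumed: one transition quarter per practice and starts two quarters apart. All 12 rows agree to within about 0.0005 (for example 0.1179 against 0.118 at a 50% initiation rate, and 0.0392 against 0.039 at a 3% completion rate). The period-adjusted design is thus worked out for initiation and completion. These figures say nothing about the implementation outcomes.

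**2. Survey outcomes.** With no intervention effect and a linear drift of d points per quarter, a pre-post change estimates d × (quarters between waves). Assume a baseline survey one quarter before the start and follow-up four quarters after it, so five quarters apart:

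| Assumed drift per quarter | Apparent effect | Share of null trials with p < 0.05 |
|---|---|---|
| 0 | 0 | about 5% |
| 0.5 points | 2.5 points | about 8% |
| 1 point | 5 points | about 18% |
| 2 points | 10 points | about 60% |

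The last column is a simulation assuming 225 parents in each wave (the article's parent total), a 50% baseline, practice-level ICC 0.026 and a simple two-sample test. The documents give neither the drift nor that test. The table shows the mechanism and is not an estimate of bias in this trial.

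**3. Counts.** Doses = eligible patients × doses per eligible patient. At a constant rate, a g% rise in patients gives a g% rise in doses. Providers recommending = providers × proportion recommending. If a practice with the planned four providers falls to three and all recommend throughout, the number drops by 1/4 = 25% while the proportion stays at 100%. Parental confidence, provider confidence and perceived barriers are survey measures, so this step does not apply to them.

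**4. Could the staggered surveys supply a concurrent control?** Take the inferred starts at quarters 2, 4 and 6.
- With waves at the start and four quarters later, the survey quarters are 2 and 6, 4 and 8, 6 and 10. Only quarter 6 is shared, so a model with categorical time rests on one FQHC against one other.
- With baseline one quarter before the start, the survey quarters are 1 and 6, 3 and 8, 5 and 10, and none is shared.

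For the shared-quarter case, the 80%-power detectable difference is 2.80 × √(2 × 0.25 × DE / n), with DE = 1 + (m − 1) × ICC for m respondents per practice. Assume a 50% proportion, ICC 0 to 0.05 and no FQHC-level variance:
- Parents, n = 75 per side, m = 25, DE 1 to 2.2: 23 to 34 points.
- Providers, n = 12 per side, m = 4, DE 1 to 1.15: 57 to 61 points.
- Naive pre-post for parents, n = 225 per wave, DE = 1: about 13 points.

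The staggering therefore offers little or nothing for the survey outcomes.

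**The case against.** The best defence is that this is a condensed article. In the Measurement and evaluation sentence, pre-post qualifies the surveys, while EHR reports are a separate source with no comparison attached. The Implementation outcomes section lists measures and desired directions, not tests. The univariate and bivariate wording belongs to the baseline section. A volume-independent vaccination outcome already exists in the primary endpoint, so doses and reminders are process measures. With 36 providers planned, a number converts readily to a proportion.

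Much of this stands. A reader might infer that doses and reminders are certain to be compared pre-post, but the text does not say so. A reader might also put a size on the volume bias by multiplying 109 patients per practice-quarter by an initiation rate of about a third. That is not supported: initiation is a patient's vaccination status, not doses given in a quarter, and second doses and ages 13–17 are left out. Nor do the documents show that everything needed is already collected. The quarterly pulls are random patient samples, not practice totals. Process data are entered by immunization navigators, who are trained as part of the intervention, so comparable control-period reminder data may not exist.

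The defence does not remove the contradiction. The article positively claims that the stepped wedge tests these outcomes, including provider recommendations, then names a pre-post survey assessment and limits the period-adjusted model to other outcomes. That is more than detail left to a fuller document. The conversion to a proportion also fails once turnover changes the number of providers from the planned 36.

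**Conclusion.** The point holds as an inconsistency between what the stepped wedge is said to test and how the implementation outcomes are assessed. As written, survey-based changes (provider recommendation and confidence, parental confidence and barriers) cannot be separated from calendar trend, and the raw numbers of providers, doses and reminders cannot be separated from staffing or patient volume.

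No reliable size of bias follows from the documents, because secular drift, volume growth and the test for these outcomes are not given; the drift table is conditional on its assumptions. It is tempting to conclude that the staggered surveys already provide a useful concurrent control. Tables 1 and 3 and Fig. 2 are not shown, the survey dates are unknown, and on the inferred schedule at most one FQHC is compared with one other. The analysis of initiation and completion is not affected.

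**What to change.** 1. Define doses as a rate per eligible patient per practice-quarter, and reminders likewise where control-period data exist. Analyse them with the structure already chosen for the HPV outcomes: quarter fixed effects, intervention, and a random practice effect, in a count model with the log of eligible patients as offset. Where reminders have no control-period data, report them descriptively.
2. Report the proportion of providers recommending, with its denominator at each wave, in place of the number.
3. Describe provider recommendation and confidence, and parental confidence and barriers, as uncontrolled pre-post changes. Limit the statements in the abstract and in the Recruitment, sample size, and retention plan so that the stepped wedge is said to test only the outcomes analysed within it.

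The cost is mainly wording, plus practice-level totals and denominators in the quarterly EHR report, which the patient samples do not supply. No survey round is added. Intervals for doses will be wider than under a naive pre-post comparison, and the claim about provider recommendations becomes weaker.
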